## Abstract

**Background:**

Globally, burns are the fifth leading cause of non-fatal children’s injuries, and the leading cause of childhood burns is hot beverage scalds. Although there have been a number of programmes aimed at preventing scalds in children, very few have specifically addressed hot beverage scalds, and fewer have reported a reduction in injury rates. In Australia, hot beverage scalds account for 18 % of all childhood burns – a figure that has remained constant for the past decade.

Innovative new technologies, such as Smartphone applications (apps), present a novel way for delivering individual-level injury prevention messages. The low cost, scalability and broad reach make this technology an ideal channel for health interventions.

One of the latest methods being used in health-related apps aimed at behaviour change is gamification. Gamification uses the gaming principles of rewards, competition and personalisation to engage participants and motivate them towards preferred behaviours.

This intervention will use a Smartphone app-based platform that combines gamification and behaviour-change strategies to increase knowledge and awareness of hot beverage scald risks and burn first aid among mothers of young children.

**Methods/design:**

This is a two-group, parallel, single-blinded randomised control trial (RCT) to evaluate the efficacy of a Smartphone app-based injury prevention intervention. The primary outcome measure is change in knowledge. Change in knowledge is measured in three components: knowledge of correct burns first aid; knowledge of the main cause of burns/scalds in children aged 0–15yrs; knowledge of the main age group at risk for burns/scalds. The secondary outcome measures relate to the gamification methods, measuring participants frequency of engagement with the Cool Runnings app. Queensland-based mothers aged 18+ years who own a Smartphone and have at least one child aged 5–12 months are eligible to participate.

**Discussion:**

To our knowledge, this is the first study to evaluate an app-based delivery of injury prevention messages, and the first study to test the efficacy of gamification techniques in an injury prevention intervention. If this intervention is found to be effective, this RCT will provide a platform for targeting other childhood injury prevention campaigns.

**Trial registration:**

This trial was registered on 14 January 2016 with the Australian New Zealand Clinical Trials Registry (ACTRN12616000019404).

## Background

In Australia, as in most developed countries, hot beverage scalds are the leading cause of burn injuries in young children. Studies from the US, Australia and the UK show hot beverage scalds account for at least 20 % of all childhood burns [1–3]. The high incidence of hot beverage scalds make it an important paediatric public health issue, yet it is often overlooked in research and injury prevention. Although there have been a number of programmes and interventions aimed at the prevention of burns and scalds in children in the past decade, very few have specifically addressed hot beverage scalds, and fewer have reported a reduction in burn and scald injury rates [4, 5]. In Australia, hot beverage scalds account for 18 % of all childhood burns – a figure that has shown no decline in the past 10 years [6]. Given the high incidence of these injuries it is essential that targeted prevention strategies are developed to curb this ongoing paediatric public health issue.

Not only are hot beverage scalds painful, they carry a risk of lifelong psychological stress and physical scarring [7–9]. As well as the physical and emotional consequences, the associated financial costs of managing these injuries on the health care system are also substantial [10]. Therefore, developing targeted prevention strategies to reduce these injuries is essential.

Innovative new technologies, such as Smartphone applications (apps), present a novel way for delivering individual-level injury prevention messages [11], and health behaviour change researchers are harnessing this technology as an intervention tool. The low cost, scalability and broad reach make this technology an ideal channel for health interventions.

The global ownership of Smartphones is growing. In 2014, 81 % of Australian adults owned a Smartphone, and the largest segment of Smartphone users are 18–34 year-olds – the age group being targeted in this intervention [12]. Smartphone ownership goes beyond socioeconomic status boundaries [13]. This medium is personal (individualised and targeted) and portable (always ‘on’), and allows for easy intervention delivery.

One of the latest methods being used in health-related apps aimed at behaviour change is gamification. Gamification is defined as ‘applying game mechanics and game design techniques in a non-game context in order to engage and influence people’s beliefs, attitudes and behaviours’ [14]. Gamification uses the gaming principles of rewards, competition and personalisation to engage participants and motivate them towards preferred behaviours.

This intervention will use a Smartphone app-based platform that combines gamification and behaviour-change strategies to increase knowledge and awareness of hot beverage scald risks and burn first aid among mothers of young children. To our knowledge this is the first study to evaluate a gamified app-based platform targeting injury prevention.

## Methods/design

### Study design

A two-group, parallel, single-blinded randomised control trial (RCT) of a technology-based education intervention (Fig. 1).

**Fig. 1 Fig1:**
[figure not shown]
Flow chart of the Cool Runnings trial

The protocol for this study has been reported according to the revised Consolidated Standards for Reporting Trials (CONSORT) guidelines [15].

### Study setting

Participants from Queensland, Australia will be recruited via online social media advertisements, specifically through Facebook and Instagram. Treatment (intervention messages) delivery will be Smartphone-based through the Cool Runnings app.

### Ethics approval

This study is registered with the Australian New Zealand Clinical Trials Registry (ACTRN12616000019404) and approved by the University of Queensland Institutional Human Research Ethics Committee (approval number: 2015001652).

### Participants

Inclusion criteria: mothers aged 18+ years of age who own a Smartphone and have at least one child aged between 5 and 12 months at enrolment.

Exclusion criteria: participants will be excluded from this study if they do not meet the inclusion criteria. However, because of the method of recruitment (voluntary response to an online advertisement), it is not possible to be 100 % confident that all participants fulfil the inclusion criteria.

### Selection bias

Selection bias is expected to be minimal because of the fact that 77 % of Australian mothers own a Smartphone [16]. Globally, mothers with children aged under 5 years are the most active on social media [17]. In Australia, 60 % of the Australian population use Facebook and the largest segment are women aged 25–34 years [12].

### Recruitment

Recruitment will be through online advertisements via social media targeted at Queensland- based mothers, aged 18+ years, who own a Smartphone (Android or Apple) and have at least one child aged 5–12 months at the time of recruitment. Facebook advertisements can be specifically targeted only to women who meet the age range, child-age range and geographic location. Potential participants will be given additional information about the study once they click on the link from the online advertisement, and can then download the free app. Participants are shown a participant information page and can consent to the study by clicking on the ‘I have read the study information and I consent to participating in Cool Runnings’. Participants are then randomised to either the control or the intervention group.

### Randomisation

Randomisation will occur through a simple randomisation table created by computer software (i.e. computerised sequence generation). Randomisation will also be stratified by maternal age (18–28 years; 29+ years), based on mean national maternal age [18].

### Blinding

The nature of this study mitigates against full blinding; however, most aspects of this RCT can be blinded. Both participant groups will download the app but are blinded to allocation. The consent form does not mention a control and intervention group (the terms ‘green group’ and ‘blue group’ are used), nor the gamification strategies for each group. Study investigators will assess the outcome data collected from the pre and post questionnaires in a blinded format. Following that point, blinding is not possible for analysing the results of the gamification strategies as they only apply to the intervention group.

All personal and identifiable participant information will be held by the platform licensor, iPug Pty Ltd, and only de-identified information will be given to the study investigators.

### Sample size

A cross-sectional study of knowledge and attitudes toward burn first aid in Queensland by Cuttle et al. [19] showed that 29 % of mothers of children aged 0–4 years in Brisbane correctly identified appropriate burn first aid (cool running water for 20 min). Assuming 90 % power and alpha = .05, in order to detect a 20 % increase in the proportion of mothers who can correctly identify the appropriate burn first aid (type and length) in the intervention group relative to the control group, 240 participants in total are required (120 each in intervention group and control group), with 95 % confidence. This will allow detection of improvement in the intervention group from 29–49 %, with no improvement in the control group.

In order to determine the proportion of participants who correctly identify the main cause of burns/scalds in children under 15 years, and/or the main age group at risk for burns/scalds, a sample size of 96 is required. This will allow detection of the true proportion in this population with 95 % CI and 10 % precision (assuming 50 % prevalence, the most conservative estimate possible). Further, in order to detect a subsequent increase in knowledge of 20 % on both these dimensions for the intervention group relative to the control group, a total sample size of 240 is required (120 in each group). Assuming 50 % loss to follow-up in each group, a total sample of 480 is required (240 intervention; 240 control).

### Intervention

Cool Runnings is an app-based platform that has been developed to implement this intervention. This RCT has an intervention group and an active control group.

#### Intervention group

During the 6-month intervention period the intervention group will receive weekly push notifications from the app inviting them to ‘Play’. Once every 3 weeks, the ‘game’ will feature one of the nine intervention messages; the format of these messages will be either an infographic, motion graphic or a 30-second video (Fig. 2). The intervention messages will focus on hot drink scald risk factors associated with a child’s age and developmental stage, and the correct burn first-aid treatment. During the 2 weeks in-between the intervention messages, participants will be given opportunities to participate in activities that continue to engage them such as posting images of safety devices around the home or answering pop quizzes. The app will record how often participants open, view and engage with the programme. The challenge is to keep participants invested in-between the actual intervention messages. Each time they participate in a ‘game’ they earn points, which means they have a better chance of earning rewards. Participants will accrue points with each full engagement, and once they achieve a certain number of points they will then be eligible to gain a reward. These rewards include shopping and movie vouchers. Participants in this group will also be able to view a ‘leader board’ so they can monitor their points that are being accrued and compare their points with other participating mothers.

**Fig. 2 Fig2:**
[figure not shown]
Content calendar for intervention and control group

#### Control group

This group will access a slightly different app interface, and will only receive three infographic messages over the 6-month intervention period (weeks 4, 10 and 16) (Fig. 2). Two of these messages will be the same as the intervention group receives (about the leading causes of burns in children, and about sharing the infant’s new developmental skills, e.g. standing, climbing, with grandparents and other caregivers). The third infographic is about childhood injuries in the home. There will be no gamification strategies, prizes or incentives offered to the control group; however, they will go in the draw to win one of two iPad Minis for completing both the pre and post questionnaires. It is hoped that the potential to win prizes will minimise loss to attrition. The app will record how often control group participants open, view and engage with the programme. At end of the intervention period the control group will be provided with the same information as the intervention group via their Smartphone app, which will be updated to include the intervention messages. A push message will be sent to participants in the control group inviting them to view the new content.

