### Data analysis

All statistical analyses will be conducted using SPSS version 23 (IBM Corporation, Armonk, NY, USA). Descriptive statistics will describe and compare the characteristics of the intervention and control group participants, and pre-knowledge difference. Chi-square analyses will be conducted in order to determine whether there is an increase in the proportion of mothers who can correctly identify the appropriate burn first aid (type and length) (component 1), the main cause of burns/scalds in children under 15 years (component 2), and/or the main age group at risk for burns/scalds (component 3), in the intervention group relative to the control group post intervention.

Increase in knowledge can also be considered a categorical variable (increase versus no increase). Cumulative incidence of increased knowledge in the intervention group versus control group will be calculated, as well as relative risk, absolute risk, absolute risk reduction and numbers-needed-to-treat. This will allow examination of the strength and magnitude of the association between the intervention and change in knowledge.

Where the sample size allows, stratified analyses will be conducted to assess the effect of the intervention in subgroups (age groups; socioeconomic status). In addition, logistic regression will be used to assess increase versus no increase in knowledge of each of the three components of the primary outcome measure. Crude and adjusted analyses will be reported. Methods such as ANCOVA will be used to assess the effect of the intervention while controlling for pre-intervention knowledge, as well a relevant (demographic) confounding factors (this may include, but is not limited to age, socioeconomic status, rurality, education, etc.). Confounding factors will be identified in the descriptive analyses.

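### As written, only the control arm is rewarded for returning the post questionnaire, so the completers compared at 6 months may be selected differently by arm

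*Protocol article*

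**What the plan says.** The Control group section of the protocol article first says that this arm gets no gamification, prizes or incentives, and then makes one exception: "they will go in the draw to win one of two iPad Minis for completing both the pre and post questionnaires". It adds the hope that prizes will limit attrition, so the draw is meant as a retention measure.

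The Intervention group section describes a different reward scheme: "Participants will accrue points with each full engagement". Enough points make a mother eligible for vouchers, and a leader board shows her standing. Neither the draw nor any other reward for the post questionnaire is mentioned there. The Data collection section says both arms complete the two questionnaires and is silent on incentives.

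The Sample size section allows for loss as follows: "Assuming 50 % loss to follow-up in each group, a total sample of 480 is required (240 intervention; 240 control"). Under Primary outcome measure, all three knowledge components come from the pre and post questionnaires, the latter at 6 months. Under Data analysis, chi-square tests examine whether the proportion correct is higher "in the intervention group relative to the control group post intervention". The same section plans crude and adjusted logistic regression on increase versus no increase in knowledge, and analyses controlling for pre-intervention knowledge and demographic factors.

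**The concern.** A mother who does not return the 6-month questionnaire has no primary outcome, so the chi-square compares whoever responds. Read literally, the reason to respond differs by arm. A control mother can win a prize for completing both questionnaires. An intervention mother is rewarded for playing, and so has a specific reason to stay only if she is engaged with the app.

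With up to half of each arm allowed to go missing, randomisation does not by itself keep the two sets of completers comparable. If the link between completing and knowing the right answer differs by arm, the difference in proportions carries a selection component. Enlarging the sample from 240 to 480 restores precision but leaves that component in place. Equal loss in the two arms would not rule it out either, because the kind of mother who completes can still differ.

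**Working it through.** **1. The plan's own figures.** Inputs from Sample size: 29% versus 49%, power 90%, alpha 0.05 (taken as two-sided), 1:1 allocation.
- Unpooled formula: n = (1.960 + 1.282)² × (0.29×0.71 + 0.49×0.51) / 0.20² = 10.507 × 0.4558 / 0.04 = 119.7, so 120 per arm. The pooled form gives 123.
- Inflation: 240 / (1 − 0.50) = 480.

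Both reproduce. The sample size is not in dispute.

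**2. What the missing half could do.** At the planned rates with half of each arm unobserved, the extreme cases for the true difference are:
- lower: 0.49×0.5 − (0.29×0.5 + 0.5) = 0.245 − 0.645 = −0.40
- upper: (0.49×0.5 + 0.5) − 0.29×0.5 = 0.745 − 0.145 = +0.60

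These are logical limits around the planned +20 points, not plausible values. They show only that the observed half does not settle the answer.

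**3. Illustration of differential selection.** The following are assumptions, not figures from the article: no true effect; the same true proportion correct p in both arms; control response unrelated to knowledge; and, in the intervention arm only, correct mothers respond at rate r1 and incorrect mothers at r0. I take p = 0.29 (the article's first-aid figure) and p = 0.50 (its conservative prevalence for the other two components).

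Observed intervention proportion = p·r1 / (p·r1 + (1 − p)·r0).

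Rejection probability of the unadjusted two-sided test at 120 completers per arm, with d the spurious difference, SE0 the pooled and SE1 the unpooled standard error: Φ((d − 1.96·SE0)/SE1) + Φ((−d − 1.96·SE0)/SE1).

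| p | r1 / r0 | Observed | d | SE0 / SE1 | Rejection |
|---|---|---|---|---|---|
| 0.29 | 0.55 / 0.45 | 0.1595/0.4790 = 0.333 | +4.3 points | 0.0598 / 0.0597 | 11.1% |
| 0.50 | 0.55 / 0.45 | 0.275/0.500 = 0.550 | +5.0 points | 0.0645 / 0.0644 | 12.1% |
| 0.29 | 0.60 / 0.40 | 0.174/0.458 = 0.380 | +9.0 points | 0.0609 / 0.0607 | 31.4% |
| 0.50 | 0.60 / 0.40 | 0.300/0.500 = 0.600 | +10.0 points | 0.0642 / 0.0639 | 34.3% |

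For p = 0.29 the response rates imply slightly fewer intervention completers (240 × 0.479 = 115 and 240 × 0.458 = 110). Using those counts changes the rejection rates only to 11.0% and 30.3%.

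**4. When there is no bias, and when the sign turns.**
- With 50% completion in both arms and the same selection in both (odds ratio of completing 2 for correct versus incorrect), both observed proportions are 0.360. The difference is zero and rejection is 5%.
- With the same odds ratio of 2 in both arms but completion of 60% in control and 40% in intervention, the observed proportions are 0.345 and 0.377: +3.2 points, rejection 8%.
- If completion is unrelated to knowledge, there is no bias. Power falls only from 89% at 50/50 completion to 88% at 60/40.
- If the selection in step 3 falls on the control arm instead, the same differences appear with a minus sign.

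**The case against.** **The draw may cover both arms.** The sentence qualifies a statement that controls get no prizes, and nothing says that intervention mothers are excluded. A reader might infer that they are deliberately shut out; a condensed article that is silent on this does not support that. If both arms are eligible, the unequal completion incentive disappears and a wording error remains. The text still needs correcting either way.

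**Baseline is adjusted for.** This stands in part. The planned adjusted analyses address the most obvious route under no effect, namely prior knowledge. They do not reach selection on engagement or on knowledge gained after baseline, and the chi-square is unadjusted.

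**Having seen the messages cannot create a false positive.** This stands. A reader might reason that engaged players saw the messages, know more and so produce a spurious effect. If the messages do nothing, seeing them makes nobody more knowledgeable. Under no effect, response must be tied to knowledge for another reason. If the messages work, retaining the more exposed mothers exaggerates a real effect, and the percentages above are then not false-positive rates.

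**The plan does more than inflate the sample.** It does: prizes are meant to reduce attrition, and the Discussion credits gamification with retention. The 50% is also a planning allowance, not an observed loss.

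**Missing-data methods belong in the statistical analysis plan.** Agreed. Their absence from the article is not part of this point.

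**Extending the draw may tilt retention the other way.** Intervention mothers would then have vouchers as well as the draw. This is a fair caution. Identical terms equalise the reward for supplying the outcome, not the total reward, so completion must still be reported by arm.

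**Conclusion.** The point holds in a limited form. Followed as written, the protocol rewards return of the primary outcome in one arm and continued play in the other, allows for 50% loss, and rests its main comparison on those who respond. Completers may therefore be selected differently by arm, and the planned adjustment may reduce this without removing it.

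Neither the size nor the direction of any bias follows from the document. The 4 to 5 points (rejection about 11 to 12%) and 9 to 10 points (about 31 to 34%) rest on assumed response rates, selection in the intervention arm alone, no true effect, 120 completers per arm and an unadjusted test. A reader might take these as the trial's false-positive rate; they are not, and equal selection with equal completion gives no bias at all. The case for acting is that the ambiguity concerns the source of the primary outcome and is cheap to remove.

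**What to change.** 1. State that the existing iPad Mini draw for completing both questionnaires covers both arms on identical terms. If it already does, correct the Control group section and say so in the Intervention group section.
2. If the terms change, tell participants through the app before the 6-month questionnaire is issued, subject to any ethics notification. The article reports 499 recruited and the trial period active, so timing matters.
3. Report questionnaire completion by arm and by baseline knowledge.
4. Support the chi-square with a sensitivity analysis of all randomised mothers, for example multiple imputation by arm using baseline answers, demographics and app use (recorded in both arms), and a second analysis setting missing 6-month answers to the baseline answer. Imputation relies on the recorded variables explaining non-response, so it tests the result and does not guarantee it.

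Cost: a lower chance of winning for each control mother, a possible ethics notification, an in-app notice and a little more analysis. No extra prizes or participants are needed.
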